#### Implementation measures

Implementation will be studied in conjunction with the effectiveness study. Clinical encounters will be evaluated through observations of video recordings, using a fidelity checklist developed in the pilot study. In addition, a survey will be administered to the staff performing the intervention. Finally, exploratory qualitative interviews will be performed with service providers and study participants to gain an understanding of their perception of TM as well as of the quality of the implementation of TM.

The implementation survey consists of three implementation outcome measures found valid and reliable in previous research [32]:

##### Acceptability of Intervention Measure (AIM)

The AIM is a four-item scale that measures the perception among implementation stakeholders that a given treatment, service, practice, or innovation is agreeable, palatable, or satisfactory. Items are rated on a 5-point scale from “completely disagree” to “completely agree”.

##### Intervention Appropriateness Measure (IAM)

The IAM is a four-item scale that measures the perceived fit, relevance, or compatibility of the innovation or evidence-based practice for a given practice setting, provider, or consumer, and/or perceived fit of the innovation to address a particular issue or problem. Items are rated on a five-point scale from “completely disagree” to “completely agree”.

##### Feasibility of Intervention Measure (FIM)

The FIM is a four-item scale that measures the extent to which a new treatment, or an innovation, can be successfully used or carried out within a given agency or setting. Items are rated on a five-point scale from “completely disagree” to “completely agree”.

### Data collection methods

#### Baseline data

Baseline data includes background variables such as age, gender, educational background, living situation, and the cognitive and functional ability of participants. Cognitive and functional ability will be measured using the MMSE [33], the Berg Balance Scale [34], and the Gait speed four-meter walking test [35]. This data will be collected by the study´s research assistants at an initial visit to the study participants home. The research assistants in the study are occupational therapists, registered nurses, or physiotherapists familiar with the process of obtaining informed consent as well as of using the baseline measurement instruments and tests.

#### Outcome data

Primary outcome data will be collected by the research team. Data on participant involvement in conversations around care, measured with the IMS, will be collected at two time points (T1, T2). T1 will be conducted directly after the needs assessment conversation and T2 will be conducted directly after the conversations about delivery of home care services. Data on service providers' efforts to involve participants in conversation will be obtained through video-recordings of the conversations. These recordings will be evaluated by the researchers using the OPTION scale.

The secondary outcome data will be collected through a survey to care managers and staff performing the intervention, consisting of the three implementation outcome measures AIM, IAM, and FIM. The survey will be administered at baseline (directly after the TM training), after 6 months, and after 12 months. Data on implementation fidelity will be obtained by evaluations of the video recorded clinical encounters, using the above-mentioned checklist.

#### Qualitative data

A qualitative approach will be used to gain an understanding of study participant and service provider experiences of using TM as well as their perceptions regarding its impact and implementation. Both individual interviews and focus groups will be conducted. Exploratory qualitative interviews will be performed with study participants individually or, when appropriate, with their relatives. Focus groups will be performed with service providers using TM. Focus group discussions and individual interviews will be audio taped and transcribed verbatim.

### Data management

Data will be processed so that unauthorized persons cannot access it. The material will be pseudonymized and stored using the University of Gothenburg's service for secure data storage for class 3 data. Security functions for class 3 data storage include two-factor authentication. Results from screening tests and outcome measures will be documented on special forms for each participant. The coded results are then entered into IBM SPSS Statistics for Windows version, 28.0 (IBM Corp., Armond, New York). The code key will be stored separately from other material. The video recordings will be transferred to secure data storage and the original files will be destroyed. When the project is finished, the collected material will be saved for a period of 10 years to enable review of the data in accordance with the University of Gothenburg's rules for handling and archiving research documents. In accordance with the Swedish Archives Act [36], the material will be archived and accessible and if the research material is not judged to have value in terms of the criteria set forth in the National Archives' regulation it will be deleted in 10 years.

### Analysis

Study data will be pooled with pilot data for analysis. To answer RQ1 and RQ2, we will perform descriptive and comparative statistical analyses as well as qualitative thematic analysis [37]. Statistical data analysis methods will be chosen based on data characteristics (e.g., ANOVA, Kruskal–Wallis). Baseline differences between groups will be controlled for in the final analyses. Sensitivity analyses will be conducted (e.g., TOT vs ITT analysis). Methods for handling missing data will be determined based on a missing data analysis to determine the nature of the missingness (e.g., MCAR). Fidelity and implementation will be tested for their impact on results. To check for comparison group equivalence, we will compare the pre-test dementia scores, functional ability and demographic variables of the two groups. When evaluating the video-recordings of the conversations, using the “OPTION scale”, inter-rater reliability will be tested. To interpret the effects of the intervention, qualitative thematic analyses [37] of the participants’ and staff’s experiences as expressed in focus group and individual interview data will be conducted.

For RQ3 we will perform descriptive analyses of survey-data as well as qualitative thematic analysis of focus group and individual interview data. This will provide analysis of patterns and themes in the interview and focus group statements. The qualitative data will enable an analysis of similarities as well as differences in the experiences of the persons involved in the study, on an individual as well as a group level. In addition, a mixed method approach [38] will be used linking descriptive statistics and qualitative analysis.

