## Methods

### Design and setting

The present study (Fig. 1) uses exploratory, descriptive, and experimental methods*.* The study will be conducted within the normal operating Swedish municipal eldercare services. The parallel group intervention study is designed as a two-armed randomized controlled trial (RCT) where the use of TM as a decision aid to support involvement in conversations regarding home care services for people with mild to moderate dementia will be evaluated through comparison with UCM. Two different situations where older people with dementia must make decisions about home care services will be studied. The first situation is a needs-assessment conversation between care managers working in eldercare and participants which concerns the follow-up of decisions about home care services. The second situation is a conversation between home care staff and participants regarding the delivery of the home care services chosen during the needs assessment. This study builds upon a previously conducted pilot study (*N* = 10) which aimed to test the intervention, study inclusion criteria, research and practice logistics, and outcome measurements prior to the full effectiveness study described here.

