### Time plan

The inclusion of participants started in November 2022. Interviews and focus groups will be conducted between January 2023 and December 2024. Inclusion as well as data collection is estimated to be completed in December 2024.

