### Allocation and blinding

Eligible participants will be randomized to either the intervention (TM) or control (UCM) group. The randomization schedule will be developed by a member of the research team not involved in participant recruitment or contact with referring agencies. The randomization sequence will be developed a priori by site (*n* = 3) using the online randomizer random.org with 50% allocation between arms. Results of the randomization for individual participants will be communicated following inclusion and collection of baseline measurement data.

Participants, service providers, and research staff will not be blinded to final participant allocation. Data collection subsequent to baseline measurements will not be blinded.

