In a previous pilot study conducted by our research team, all TM materials and procedures were adapted in collaboration with service providers in one of the municipalities participating in the present study. In addition, specific TM material was developed and adapted for the purpose of the present study. The specific topics and range of options within each topic for use within the TM framework have been identified in workshops with service providers using the World Health Organization’s International Classification of Functioning (ICF; [27]) and in line with the systematic needs-assessment tool “The Individual’s Needs in the Center” (IBIC) [28]. The material and procedures to be used in the present study have been tested, revised, and re-tested several times in preparation for this study. In September 2020, researchers and service providers tested the TM with older adults (acquaintances and/or service users). Subsequently, care managers, home care staff, and researchers tested and revised the TM material in reoccurring workshops held between autumn 2020 through 2021. All instructions and TM materials have been gathered in binders which have been provided to all care managers, home care staff, and research assistants involved in the study. All service providers and research assistants involved in the pilot study as well as the present study have received a two-day training in the use of TM from accredited TM trainers at the Dart Communication and Data Resource Centre, Region Västra Götaland, Sweden.

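### Pooling the 10 pilot participants into the TM versus UCM analysis, with no separation by study phase, can bias or dilute the randomised comparison for little gain in precision

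*Protocol article*

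**What the plan says.** The Analysis section opens with "Study data will be pooled with pilot data for analysis". The next sentence introduces the analyses for RQ1 and RQ2. Nothing limits the pooling to RQ3 or to the qualitative material. The only sensitivity analysis given as an example is TOT against ITT.

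Other sections describe the pilot and the trial as follows:

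- **Design and setting:** a pilot of N = 10 had already been conducted. It "aimed to test the intervention, study inclusion criteria, research and practice logistics, and outcome measurements prior to the full effectiveness study described here".
- **TalkingMats (TM) intervention:** TM materials and procedures were adapted in the pilot with providers from one of the three municipalities, and further material was made for the present study. "The material and procedures to be used in the present study have been tested, revised, and re-tested several times".
- **Allocation and blinding:** "The randomization sequence will be developed a priori by site", with equal allocation at three sites.
- **Time plan:** "The inclusion of participants started in November 2022".
- **Implementation measures:** the fidelity checklist came out of the pilot. The Analysis section then plans to test the impact of fidelity on the results.

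The article does not say how the 10 pilot participants were allocated, which version of the material they met, whether all 10 satisfy the final eligibility criteria, or whether they count toward the planned 50 per arm.

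**The concern.** RQ1 and RQ2 are answered by a comparison whose validity rests on the trial's random allocation. The 10 pilot participants come from an earlier, developmental phase, and the allocation procedure described in the article does not reach them. If they differ from trial participants on average, and are not spread evenly over the arms, that difference enters the estimated effect of TM. If they are spread evenly but were seen with a less effective version of TM, the estimate is pulled toward zero and no longer describes the final procedure.

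The article states the pooling as a rule. An analysis plan that based the primary comparison on trial participants alone would contradict that rule, so the sentence itself needs to change. Adjusting for measured baseline differences, which the Analysis section does plan, does not replace random allocation, and it does not deal with differences in material or calendar time.

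**Working it through.** **Inputs from the article.** Pilot 10 (Design and setting). Planned 50 per arm, effect size 0.25, power 0.9, p = 0.05 (Recruitment and eligibility criteria). 1:1 allocation (Allocation and blinding).

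**Assumptions, because the article gives no figure.** Of the 10 pilot participants, *k* used TM, with *k* = 5, 7 or 10. Pilot participants differ from trial participants by *δ* = 0.5 to 1.0 SD on the outcome, equally in both arms. The sign of *δ* is unknown and the bias takes the same sign. Unit SD, two-sided 5% test, normal approximation.

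**1. The plan's own sample size.** It is not reproduced by a simple two-arm comparison. Read as a standardised mean difference, 0.25 needs 2 × (1.960 + 1.282)² / 0.25² ≈ 337 per arm. Read as Cohen's *f* (a mean difference of 0.5 SD), it needs 85 to 86 per arm. The article does not name the metric. This is a separate matter and does not affect the steps below, which use only the planned 50 per arm.

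**2. Share of the pooled data.** 10/110 = 9.1% if the pilot is added to the 100, or 10/100 = 10% if it is counted within them.

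**3. Bias with the 10 added to 50 + 50.** The arms become 50 + *k* and 60 − *k*.

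Bias = *δ* × [*k*/(50 + *k*) − (10 − *k*)/(60 − *k*)]

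SE = √[1/(50 + *k*) + 1/(60 − *k*)]

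Type I error = Φ(−1.96 − bias/SE) + 1 − Φ(1.96 − bias/SE)

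| Pilot split TM/UCM | Bracket | Bias, *δ* = 0.5 | Bias, *δ* = 1.0 | Type I error |
|---|---|---|---|---|
| 5/5 | 5/55 − 5/55 = 0 | 0 | 0 | 0.050 |
| 7/3 | 7/57 − 3/53 = 0.066 | 0.033 SD | 0.066 SD | 0.053 to 0.064 |
| 10/0 | 10/60 − 0 = 0.167 | 0.083 SD | 0.167 SD | 0.072 to 0.140 |

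**4. If the 10 sit within the 100** (50 per arm in total). An all-TM pilot gives *δ* × 10/50 = 0.10 to 0.20 SD, with type I error 0.079 to 0.170. A 7/3 split gives *δ* × (7 − 3)/50 = 0.04 to 0.08 SD, with type I error 0.055 to 0.069.

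**5. Dilution with a 5/5 pilot.** If the version used in the pilot had a fraction *g* of the final effect, the pooled effect is (50 + 5*g*)/55 of the true one: 0.91 for *g* = 0 and 0.95 for *g* = 0.5.

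**6. What pooling buys.** The detectable difference at 90% power is (1.960 + 1.282) × √(2/*n*). With *n* = 50 per arm it is 0.648 SD, and with *n* = 55 it is 0.618 SD. For an all-TM pilot (60 and 50) it is 3.242 × √(1/60 + 1/50) = 0.621 SD. The gain is about 0.03 SD in each case.

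**The case against.** The strongest reply is that the harm is conditional. The pilot may have had its own 1:1 randomisation. With a 5/5 split, a shift common to both arms leaves the contrast unbiased, and weaker material only dilutes the effect, which is conservative for a superiority claim. A phase-stratified pooled analysis would then be defensible, and excluding the pilot would be a preference. The article also says that providers and research assistants in both phases received the same two-day training, that baseline differences will be controlled for, and that fidelity will be examined. Its sensitivity analyses are an open list, and details of the pilot could stand in the full protocol or analysis plan.

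Much of this stands, and it rules out several stronger readings that a reader might infer:

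- *The pilot was not randomised.* The article is silent on how it was allocated.
- *The 10 received older material.* This is plausible from the account of repeated revision, but nothing dates the 10 against those revisions.
- *The decision to pool was made with knowledge of the pilot results.* The article says that outcome measurement was tested. It does not say that outcomes were compared by arm or used in choosing the analysis.
- *The worst case equals a third of the target effect.* That divides 0.083 by 0.25 and needs 0.25 to be a standardised mean difference. If it is Cohen's *f*, the target is 0.5 SD and the ratio is one sixth.

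The reply does not remove the rule itself. Pooling is stated without qualification for the primary comparisons. None of the listed safeguards separates the phases, and the open list commits to no analysis without the pilot.

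**Conclusion.** The point holds in conditional form: pooling *can* bias or dilute the randomised comparison, but the article does not show that it does. Under the assumed shifts the consequence runs from no bias (balanced pilot, common shift), through a loss of about 5 to 9% of the effect (balanced pilot, weaker or ineffective version), to 0.08 to 0.17 SD with type I error up to about 0.14 when an all-TM pilot is added to the 100. The upper end needs both an all-TM pilot and a large shift, and neither is documented. The case for change rests on the balance: an avoidable risk to the primary comparison is taken for a gain of about 0.03 SD in detectable difference. Should-fix, with medium confidence, since the size depends on facts about the pilot that the article does not give.

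**What to change.** Replace the pooling sentence in the Analysis section with:

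> *The primary analysis of RQ1 and RQ2 includes only participants randomised under the present trial's sequence; pilot participants are reported separately, and a pooled analysis stratified by study phase is a sensitivity analysis only.*

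State alongside it how the 10 pilot participants were allocated, which version of the material they received, and whether they count toward the 100. If all 10 were in one arm, the phase-stratified analysis draws no information on the contrast from them, so the split determines whether that sensitivity analysis is worth running.

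The cost is a change of wording and at most 10 records leaving the primary analysis. If the 10 were additional to the 100, the detectable difference is 0.65 rather than 0.62 SD. If they were counted within the 100, either 10 more participants are randomised or the primary analysis has 90, for which the balanced case gives 3.242 × √(2/45) = 0.68 SD instead of 0.65.

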### Recruitment and eligibility criteria

The target group for this study is older people with mild to moderate dementia who use home care services provided by municipal eldercare authorities. Service users will be identified by care managers, healthcare staff or a specialized dementia team. At first contact, potential participants will receive brief information about the study and be offered the opportunity to participate in screening tests for mild to moderate dementia. It will be made clear that the choice to participate in the study (or not) will not affect receipt of eldercare. On expression of interest to participate in the study, permission will be sought by home care service providers to forward contact details to the research team. A research assistant will contact individuals referred to the study to arrange a convenient time to meet. At this visit, written and verbal informed consent will be obtained, and baseline data will be collected.

Eligibility criteria:Participants are aged 65 or older.Participants receive home care services from the eldercare authority in one of the three participating municipalities.Participants are assessed as having mild to moderate dementia which is defined as scoring between 12–23 on the mini-mental state examination (MMSE).

According to preliminary power calculations, we plan to include 50 participants in each study arm. The calculation was made based on what is needed to detect a moderate difference (0.25 effect size) with 0.9 power, p = 0.05 [25]. Significant differences over time in involvement were found using the Involvement Measure Scale (IMS) in a sample of 18 in a previous study [11].

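### Covariate adjustment is tied to baseline differences seen between the arms, which makes the model data-dependent and gives up the precision of a prognostic covariate that is always included

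*Protocol article*

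**What the plan says.** The Analysis section of the protocol article states that "Baseline differences between groups will be controlled for in the final analyses". The same paragraph adds: "To check for comparison group equivalence, we will compare the pre-test dementia scores, functional ability and demographic variables of the two groups". No threshold for a difference is given, and no covariate is named.

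The Baseline data section lists what is available: "background variables such as age, gender, educational background, living situation, and the cognitive and functional ability of participants". The cognitive and functional tests are the MMSE, the Berg Balance Scale and four-metre gait speed. MMSE is also an eligibility criterion (12 to 23), so every participant has a score. Under Allocation and blinding, the randomisation sequence is built by site for three sites.

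Under Outcome data, the IMS is taken only after each of the two conversations, so there is no baseline score of the primary outcome to adjust for. The choice of statistical method is also left to the characteristics of the data, with ANOVA and Kruskal–Wallis as examples.

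**The concern.** Under randomisation, a baseline difference between arms is a chance event. Finding one says little about whether the variable is worth adjusting for. The benefit of a covariate comes from its correlation with the outcome, and that benefit is present whether or not the arms happen to differ on it.

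A rule that adjusts only after a difference is seen has two consequences. First, a prognostic variable is left out of the model most of the time, so its precision is lost. Second, the final model is not known until the data are in. With no threshold stated, someone must judge what counts as a difference, in a trial where research staff know the allocation. At stake are some power and the clarity of a fixed primary model. The validity of a strictly applied analysis is not at stake.

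**Working it through.** **Inputs from the protocol article.** 50 per arm, effect size 0.25, power 0.9, p = 0.05 (Recruitment and eligibility criteria); 1:1 allocation, three sites (Allocation and blinding).

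**Assumptions.** The metric of the 0.25 is not stated. I read it as Cohen's f, so d = 2 × 0.25 = 0.5 for two equal groups, tested two-sided. The MMSE–outcome correlation r is not in the article, so I use 0 to 0.5.

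**The plan's own figure.** For a simple two-group comparison, 0.25 read as d needs 337 per arm for 90% power. Read as f it needs 85 to 86 per arm. With 50 per arm, power is about 0.24 and 0.70 respectively. A total near 100 appears only for a two-time repeated-measures comparison with a T1–T2 correlation of roughly 0.1 to 0.2, which the article does not state. That mismatch is a separate matter. Here 0.70 is only the reference point.

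**Power with MMSE always included.** Adjustment multiplies the residual variance by 1 − r², so the standardised effect becomes d/√(1 − r²). With n = 50 per arm the noncentrality is

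λ = 0.5 × √(50/2) / √(1 − r²) = 2.5 / √(1 − r²).

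The normal approximation to power is Φ(λ − 1.96). The last column uses the noncentral t.

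| r | 1 − r² | λ | Φ(λ − 1.96) | noncentral t |
|---|---|---|---|---|
| 0 | 1.00 | 2.500 | 0.705 | 0.697 |
| 0.2 | 0.96 | 2.552 | 0.723 | 0.714 |
| 0.3 | 0.91 | 2.621 | 0.746 | 0.737 |
| 0.5 | 0.75 | 2.887 | 0.823 | 0.815 |

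Spending three degrees of freedom (one for MMSE, two for three sites; 98 falls to 95) changes the t-based figures only in the fourth decimal.

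**Power under an imbalance rule.** This was simulated with 10,000 trials per setting, 50 per arm and no site effect. There were seven independent baseline variables (MMSE, Berg, gait speed, age, gender, education, living situation), of which only MMSE was prognostic. A variable was adjusted for only if its baseline comparison gave p < 0.05. That 5% threshold is my assumption.

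| | r = 0.3 | r = 0.5 |
|---|---|---|
| Power, no adjustment | 0.704 | 0.701 |
| Power, imbalance rule | 0.697 | 0.703 |
| Power, MMSE always included | 0.736 | 0.811 |
| SD of estimate, imbalance rule | 0.196 | 0.194 |
| SD of estimate, MMSE always included | 0.188 | 0.174 |
| Type I error, imbalance rule | 0.044 | 0.042 |

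MMSE enters the model in about 5% of trials, as a 5% test implies. At least one of the seven variables triggers adjustment in about 30% of trials; by arithmetic, 1 − 0.95⁷ = 0.302. The mean estimate is 0.50 under every approach when the true difference is 0.5, so there is no bias.

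If an analyst were free to report the best of the unadjusted, MMSE-adjusted and imbalance-adjusted results, type I error would be 0.062 at r = 0.3 and 0.075 at r = 0.5. The article does not describe such a practice. These figures only mark what the open threshold could allow.

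**The case against.** The strongest reply is that the mechanism is partly inferred. The article never says that the equivalence check selects the covariates, and it names neither a significance test nor a cut-off. A looser criterion would bring MMSE into the model more often than the simulation shows. This stands: the 5% inclusion rate and the simulated 0.70 belong to an assumed version of the rule. The reading itself survives, because what is to be controlled for is differences between groups, not the baseline variables as such.

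A second reply is that an analysis plan, not shown here, could name the covariates. The missing list is indeed no fault of a condensed article. The point is the selection rule that the article does state, which such a plan would have to replace.

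Third, a reader might infer that MMSE is an obvious predictor of both outcomes and that the power loss is therefore large. The article does not support that. It gives no correlation. OPTION rates the effort of the service provider, not the participant's ability, and entry is limited to MMSE 12 to 23, which may weaken any correlation. At r = 0.2 the gain is about 2 points, and at r = 0 it is nil.

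Fourth, a reader might infer that the rule biases the result or inflates false positives. Strictly applied, it does neither.

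Finally, the analysis pools data from a pilot (N = 10), and the article does not say whether the pilot was randomised. Differences in the pooled set need not be pure chance, so describing the arms at baseline remains useful. That does not justify using the description to choose covariates.

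**Conclusion.** The point holds in a moderate form. On the natural reading of the Analysis section, adjustment depends on imbalance observed between the arms. For the randomised comparison this is inferior to fixing covariates in advance: the model becomes data-dependent, and the precision of an always-included prognostic covariate is forgone.

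On the assumptions d = 0.5, 50 per arm and a two-sided 5% test, always including MMSE gives power of about 0.70 (r = 0), 0.72 (r = 0.2), 0.74 (r = 0.3) and 0.82 (r = 0.5). An imbalance rule with an assumed 5% threshold gives about 0.70. The correlation is unknown, so the gain lies anywhere from nothing to about 12 points over this range, and it may be smaller for OPTION. The case for change rests on a fixed model at almost no cost, with a possible gain in power.

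**What to change.** Replace the sentence on controlling for baseline differences, and revise the equivalence-check sentence to match, with wording such as:

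> The primary IMS and OPTION comparisons use a regression (ANCOVA-type) model adjusting for baseline MMSE (continuous) and site, whatever the observed balance. Baseline characteristics are tabulated by arm without significance tests and do not determine the covariates.

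Site belongs in the model because the sequence is built by site. If a rank-based test such as Kruskal–Wallis is kept, it should be a sensitivity analysis, since it takes no covariates.

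No new data are needed, as MMSE and site are known for every participant. The cost is about three degrees of freedom in 100 participants and a commitment to a covariate model, which narrows the choice of method that the article now leaves open.

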### Participant timeline

Study participants will be offered the screening test within two weeks from their first contact with research staff (Fig. 2). Following screening, study participants will be randomized to TM or UCM. Two weeks following screening, participants will have a needs assessment conversation with a care manager. Approximately three weeks post conversation with care managers, a meeting with home care service staff will take place. Directly following participants' conversation with care managers and home care staff, a researcher will conduct a standardized interview using the IMS. In 2023 or 2024, participants as well as their relatives will be invited to take part in qualitative interviews with one of the researchers.

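### The missing-data method is to be selected by an analysis meant to establish the missingness mechanism; observed data cannot establish it, so the assumption and method should be fixed in advance

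*Protocol article*

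**What the plan says.** The Analysis section of the protocol article gives one sentence on missing data: "Methods for handling missing data will be determined based on a missing data analysis to determine the nature of the missingness (e.g., MCAR". MCAR is the only mechanism named, and only as an example. The section names no test, no threshold and no method attached to any result. Its one example of a sensitivity analysis contrasts TOT with ITT, which does not address the missingness assumption.

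The outcomes that can be missing are described elsewhere. Under Outcome data, the IMS "will be collected at two time points (T1, T2", once after each conversation, and OPTION is scored from video recordings of the same conversations. Under Participant timeline: "Approximately three weeks post conversation with care managers, a meeting with home care service staff will take place". The size is set under Recruitment and eligibility criteria: "we plan to include 50 participants in each study arm". The Analysis section adds: "Study data will be pooled with pilot data for analysis". No missing rate is given.

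**The concern.** A condensed article may leave the details of missing-data handling to an analysis plan, and silence on them would be no finding. Here the article is not silent. It states how the method will be selected, and the selection depends on learning something the data cannot reveal. An analysis plan that carried out this sentence faithfully would inherit the fault.

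The T2 comparison is the one most exposed. It comes about three weeks after T1, participants score 12 to 23 on the MMSE, and allocation is open to participants, providers and research staff. Loss at T2 that is related to T1 involvement, and differently so by arm, is plausible. A check that fails to find this could be taken as licence for an analysis that assumes it away.

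**Working it through.** **1. What the data can identify.** Let R = 1 if T2 is missing. The data give the distribution of T1 and R, and of T2 given T1 when R = 0. They say nothing about T2 given T1 when R = 1.
- Set that unseen distribution equal to the seen one, and the mechanism is MAR.
- Shift it by any delta other than zero, and the mechanism is MNAR.
- Both fit the observed data identically, at any sample size and any missing rate. Only MCAR has a testable consequence, namely that T1 and baseline are alike for R = 0 and R = 1. That consequence can be rejected but not proved.

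**2. Sample size available for such a check.** The sentence on missing data has no figure of its own to reproduce. The design gives 2 × 50 = 100 participants, or 100 + 10 = 110 if the pilot participants are additional.

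**3. How often an MCAR check detects dependence.** The statistic is d² = Σ over groups (missing, observed) of n_g (x̄_g − x̄)′ S⁻¹ (x̄_g − x̄), referred to chi-square with k degrees of freedom at 0.05. One of the k complete variables drives missingness. There were 1,500 runs per cell. Missing rates and odds ratios (OR) per SD are assumptions. Detection at N = 100:

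| Missing | OR | k = 1 | k = 5 | k = 7 |
|---|---|---|---|---|
| 5% | 1.5 | 15% | 9% | 8% |
| 5% | 2 | 29% | 15% | 13% |
| 5% | 3 | 58% | 32% | 29% |
| 10% | 1.5 | 19% | 11% | 10% |
| 10% | 2 | 52% | 26% | 20% |
| 10% | 3 | 84% | 59% | 51% |
| 20% | 1.5 | 36% | 19% | 15% |
| 20% | 2 | 75% | 47% | 39% |
| 20% | 3 | 97% | 86% | 78% |
| 30% | 1.5 | 42% | 22% | 18% |
| 30% | 2 | 84% | 57% | 51% |
| 30% | 3 | 99% | 94% | 90% |

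Baseline offers about 5 to 7 such variables. For k = 5 or 7, OR 1.5 to 2 and 5 to 20% missing, detection is 8 to 47%, so 53 to 92% is missed. For OR 3 with at least 20% missing, detection is 78 to 94%. At N = 110 detection rises by at most about 9 points.

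**4. When missingness depends on the unseen T2 score.** With 10 to 30% missing, OR 2 or 3 and T1–T2 correlation 0 to 0.5, a six-variable check rejected MCAR in 4 to 28% of trials. The complete-case T2 mean was off by 0.06 to 0.27 SD. This is the error in a mean, not in the arm difference.

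**5. What complete cases would do to the T2 arm difference.** Suppose dropout depends on standardised T1 (z) in one arm only, with p(z) = 1/(1 + exp(−(a + bz))) and missing rate m in that arm. With no treatment effect and T1–T2 correlation ρ:

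bias = ρ × E[z | observed], where E[z | observed] = ∫ z(1 − p(z))φ(z)dz / (1 − m).

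- b = −0.5, m = 15%: E = 0.073; × 0.5 = 0.036 SD.
- b = −1.0, m = 20%: E = 0.173; × 0.7 = 0.121 SD.
- b = −1.0, with a left at logit(0.20), so that the affected arm loses about 24%: E = 0.204; × 0.7 = 0.143 SD.

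The range is therefore 0.04 to 0.12 SD with the rate held at 15 to 20%, and up to 0.14 SD if the steeper slope also raises the rate in that arm. If the dependence is the same in both arms, the two shifts cancel; simulation gave at most 0.004 SD.

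**6. Scale.** With 80 to 85 complete cases, the standard error of the T2 difference is √(2/42.5) = 0.217 to √(2/40) = 0.224 SD. The bias is thus roughly 0.04/0.217 = 0.2 to 0.14/0.224 = 0.6 standard errors. The planned effect is 0.25 in an unstated metric. Read as a standardised difference, the bias is 16 to 56% of it (0.04/0.25 to 0.14/0.25). Read as f, which corresponds to a difference of 0.5, it is 8 to 28%.

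**The case against.** The strongest reply is that the sentence is loose wording rather than a decision rule. It is compatible with describing missingness patterns, finding their predictors and then choosing imputation variables, with the rest left to an analysis plan. Part of this stands: describing patterns is good practice, and nothing shows that a crude test would be applied mechanically. But the sentence makes the choice of method depend on determining the mechanism, and that step fails however it is carried out.

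A reader might infer four stronger things that the document does not support:
- **That the check would usually point to MCAR for lack of power.** This depends on assumed rates and slopes. It fails for strong dependence with at least 20% missing, and for OR 2 with at least 10% missing when only the driving variable is tested (52 to 84% detected). Dependence in one arm is also easier to find if looked for within that arm: at a slope of −1.0, 60 to 72%, against about 36 to 47% when arms are pooled.
- **That complete-case analysis would follow.** The article names no such step.
- **That T1 scores of those missing at T2 would be discarded.** Nothing says so, and a T1 comparison could use them all.
- **That the method would be chosen after seeing the treatment effect.** The sentence conditions on missingness, not on the arm comparison, and gives no timing.

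**Conclusion.** The sentence is wrong as written, and the point is minor. The core of it needs no assumption: no analysis of the observed data can determine the nature of the missingness beyond possibly rejecting MCAR. That non-rejection is weak evidence at 100 to 110 participants holds for weak to moderate dependence and for the MNAR cases tried, but not for strong dependence with substantial loss.

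The bias of about 0.04 to 0.14 SD is conditional on three things the article does not state: that non-rejection leads to complete cases, that dropout depends on T1 differently by arm, and that rates, slopes and correlation lie in the assumed ranges. If dependence is equal in both arms, the cost is mainly precision.

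**What to change.** Replace the sentence with a pre-specified assumption and method, for example:

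*Missing IMS and OPTION scores are handled under MAR given arm, site, baseline MMSE, function and observed outcomes, by multiple imputation by arm (or by a likelihood-based model of T1 and T2 if that is the primary model), including all randomised participants. Sensitivity: delta-shifted imputation over a stated range. Missingness patterns are described, but no mechanism test selects the method.*

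The likelihood-based option is conditional because the article offers only ANOVA and Kruskal–Wallis as example analyses. OPTION is included because it is a primary outcome too and can be missing when a recording is. The delta range must be given as numbers. The baseline variables needed are already being collected, so the cost is wording and modest analyst time.
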